#### Aim 2.

The primary analyses will evaluate differences between baseline and plateau phase in brain activation to visual food cues, specifically: 1) meal-induced change in mean extracted parameter estimates across all *a priori* satiety regions (high-calorie food vs. objects), 2) changes in pre-meal activation (high-calorie food vs. objects) from each of the four inhibitory control and reward modulation regions, and 3) associations of any findings with changes in Aim 1 metabolic outcomes. Outcomes for secondary analyses include mediobasal hypothalamic T2 relaxation time (vs. control regions) and meal-induced changes in salience network connectivity. Associations with weight regain post-plateau will be explored as will within-subject differences in regions outside *a priori* ROIs via fully adjusted voxel-wise comparisons. For within-subject comparisons, we will use linear mixed models that can accommodate repeated measures as well as missing data. Relationships between neurophysiologic measures and behavioral and hormonal correlates will be assessed using linear regression of change in behavioral correlates from baseline to plateau, as a function of each measure separately and together as covariates (i.e., changes in satiety response and inhibitory control activation), adjusting for time between plateau and baseline and, as needed, baseline covariates that are potential confounders such as sex, age, and % body fat. A sample size of N = 43 at plateau maintains 80% power to detect within subject differences in brain activation to visual food cues.

#### Aim 3.

The primary outcomes of interest being explored in Aim 3 are entry into a weight loss plateau (Yes/No) and time from baseline (beginning of behavioral weight loss program) to plateau entry (continuous). Entry into a weight loss plateau will be defined as the 1) day at which a subject met weight loss plateau criteria during real-time monitoring or 2) first day of a weight loss plateau identified via threshold regression modeling at study completion. *A priori* predictors of interest for Aim 3 are based on available literature and our own findings and include the slope of the first active weight loss period [64]; trends over time in craving for carbohydrates/starches, dietary restraint, and disinhibition [65]; changes in T-cell and muscle maximal respiratory capacity; fasting ghrelin [66]; and baseline central satiety response, mediobasal hypothalamic T2 relaxation time [67], leptin [28] concentrations, and HOMA-IR [68]. Other predictors (i.e., inhibitory control) may be tested based on the findings of Aims 1 and 2; remaining predictors will be considered exploratory. Analyses will include only participants who achieved active weight loss. Fully adjusted models will include baseline or change in % body fat. Sensitivity analyses will be completed to evaluate whether excluding participants not achieving adherence will have the same or better predictive capabilities. A sample size of N = 40 participants who achieve active weight loss provides 91% power to detect effect sizes of R^2^ ≥ 0.36 at P < 0.05 for continuous outcomes.

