The overarching hypothesis of ADAPT is that an involuntary weight loss plateau is characterized by accentuated changes in bioenergetics and neuro-physiology that thwart efforts at additional weight loss and, ultimately, favor weight regain [Fig 1]. ADAPT also investigates predictors of entering into a weight loss plateau that could be mechanistically related to cessation and/or the degree of weight loss in response to behavioral weight loss. To investigate these hypotheses, the study implements a remotely delivered group behavioral weight loss program augmented by individual support to stimulate weight loss. We combine this program with real-time monitoring and individually timed outcome assessments to study 90 adults with obesity at baseline, and re-evaluating those who enter active weight loss and plateau phases, as defined by the study protocol. The specific aims of this research are threefold: 1) to test if an involuntary weight loss plateau is distinguished metabolically from other phases of weight loss by alterations in cellular bioenergetics across multiple tissue types, 2) to test for neurophysiologic changes consistent with reduced satiety at a weight loss plateau and their relation to metabolism, and 3) to explore predictors of a weight loss plateau. We hypothesize that peripheral blood mononuclear cells, myofibers and adipocytes obtained during the plateau phase will show reductions in mitochondrial respiratory capacity and/or improved coupling relative to baseline and active weight loss. We further hypothesize that the central satiety response will be reduced from baseline at a weight loss plateau, activation in inhibitory control regions involved in self-regulation will be enhanced, and both will correlate with suppressed tissue-level and whole-body metabolism [Fig 1]. Finally, we hypothesize that our exploratory predictive analyses will identify potential behavioral, neurophysiologic, and bioenergetic predictors of early entry into an involuntary weight loss plateau that would be appropriate targets for future research or interventions.

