### Remote weighing and real-time classification of phase of weight loss

A cornerstone of the ADAPT study design is the use of daily weighing to define the weight-loss phases in real time and schedule study assessments that align with participants’ individual periods of active weight loss and/or a weight loss plateau. Throughout the enrollment period, all participants are asked to weigh themselves daily on a study-provided electronic scale (BodyTrace™). Daily weights are remotely transmitted and monitored by the study. Participants are instructed to weigh themselves daily upon waking (fasted) and after voiding. Baseline weight is calculated as the average daily weight over the ~ 7-day period after the baseline visit, but before the start of the behavioral weight loss program. The baseline weight is used to calculate the daily percentage body weight change from baseline in real time.

Our pre-defined study criterion for active weight loss is based on the typically recommended pace of weight loss in a behavioral weight loss program and is defined as a rate of ≥0.5 lb/week. A weight loss plateau is defined as a rate within ±0.25 lbs/week. For each participant, daily percent weight change relative to baseline weight is calculated, and participant-specific slopes are derived that convert these percent changes into pound-per-week-equivalent rates aligned with the pre-defined study criteria for active weight loss and weight loss plateau.

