### Statistical analysis plan

#### Aim 1.

Primary outcomes are oxidative phosphorylation and maximal respiratory capacity in T-cells, and permeabilized muscle fibers, the latter with fatty acid oxidation and complex I substrate. Secondary outcomes include T-cell and permeabilized muscle fibers uncoupling (proton leak respiration), adipose tissue mitochondrial respiratory capacity and coupling, UCP-1 expression, and inflammatory and lipolytic markers. As a prelude to inferential testing, linear regression will assess change in each measure as a function of potential confounding baseline covariates including % body fat, age, and sex as well as resting energy expenditure. Linear mixed models (adjusted for baseline confounders if needed) will be used to test for a main effect of time (baseline, active weight loss, plateau), followed by Bonferroni-adjusted formal *post hoc* testing to assess differences between phases and evaluate if a weight loss plateau represents a distinct metabolic state. We will then explore *evidence of cross talk* among T-cells, muscle, adipose tissue, and brain measures of appetite (See Aim 2 below). For measures that are changed from baseline by weight loss, we will perform linear regression amongst outcomes of the change from baseline to active weight loss or weight loss plateau. *Implications for weight maintenance* will be explored via linear regression of % weight change from plateau to 18 mo. as a function of the change in primary and secondary metabolic measures at plateau phase from baseline, adjusting for time between plateau and end of follow-up. Secondary analyses will use values measured at plateau (not change). Stratified analyses will assess sex as a biological variable. A sample size of N = 40 at active weight loss and plateau provides 99% power to detect within-subject differences between baseline and plateau and end of follow up for primary outcomes.

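### Aim 3's plateau entry (Yes/No) has two unreconciled definitions and no time horizon; under the real-time one, nearly every fully followed active loser scores Yes

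*Protocol article*

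**What the plan says.** Aim 3 of the statistical analysis plan states: "The primary outcomes of interest being explored in Aim 3 are entry into a weight loss plateau (Yes/No"). The second outcome, in the same sentence, is the time from the start of the program to entry. Entry is either the "day at which a subject met weight loss plateau criteria during real-time monitoring" or the "first day of a weight loss plateau identified via threshold regression modeling at study completion". The two are joined by a bare 'or', and no time limit is given. Only participants who achieved active weight loss are analysed. The stated power is 91% for R² ≥ 0.36 at P < 0.05 with N = 40, for continuous outcomes.

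The rules are in the section on remote weighing. Active loss "is defined as a rate of ≥0.5 lb/week". For the plateau: "A weight loss plateau is defined as a rate within ±0.25 lbs/week". Both are judged on a rolling slope over the preceding 21 days, and a plateau counts only after active loss. Weights are monitored for 18 months. The same section says that statistical analyses use the final phase assignments, which come from threshold regression; that sentence concerns the phase at in-person visits.

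The Introduction hypothesises that the study will find "predictors of early entry into an involuntary weight loss plateau". It also says that loss typically plateaus at about 7–10% of body weight and that regain is common. The Fig 1 legend says only that a substantial percentage will plateau. No plateau rate or dropout rate is given.

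**The concern.** A binary outcome needs both values in useful numbers. Here the analysis set is people who have already lost at 0.5 lb/week or more. The real-time definition then asks whether a noisy three-week slope ever falls inside a narrow band around zero during about 78 weeks. A curve that stops falling, or turns upward, passes through that band. A curve that keeps falling can be put there by noise alone.

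If nearly everyone scores Yes, a model for the outcome has almost nothing to explain, and the few No values reflect mostly how long a person kept weighing. The other definition, threshold regression, can return No for someone the real-time rule calls Yes. The result of a primary Aim 3 analysis would then depend on an unstated choice between the two.

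**Working it through.** **1. The plan's own figure.** R² = 0.36 gives f² = 0.36/0.64 = 0.5625. With N = 40 the noncentrality is 0.5625 × 40 = 22.5. The overall F test at 0.05 then has power 92.2% with 6 predictors and 89.8% with 7. The number of predictors is not stated, but 91% is reproducible. It applies to a continuous outcome; no figure is given for Yes/No.

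**2. Noise of the 21-day slope.** For 21 daily weights, the sum of squared deviations of the day index is 21 × (21² − 1)/12 = 770. The slope's standard error per week is 7 × SD/√770 = 0.252 × SD. The daily SD is not in the document. For assumed SDs of 1, 1.5 and 2 lb the standard error is 0.25, 0.38 and 0.50 lb/week. That equals or exceeds the band's half-width of 0.25 lb/week.

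**3. Real-time definition, complete follow-up.** The rule was applied daily for 78 weeks: active slope after week 4, then any later 21-day slope within the band. Baseline weight (240 lb), daily SD and curve shapes are assumptions.

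| Curve after active loss | Share scoring Yes |
|---|---|
| Flattening, slowing to 0.35 lb/week, or regaining 0.6 lb/week (SD 0.6–2 lb) | 99.9–100% |
| Sharp regain of 1.5 lb/week (SD 1–2 lb) | 99.6–100% |
| Steady loss of 0.75 lb/week, no plateau (SD 1–2 lb) | 99.7–100% |
| Steady loss of 1 lb/week, no plateau | about 36–38% at SD 1 lb; 99% at 1.5; 100% at 2 |

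At an SD of 0.6 lb, steady losers of 0.75–1 lb/week mostly escape. Such people would be rare by the document's own expectation. Even 0.5 lb/week held for 78 weeks is 39 lb, or 39/240 = 16%, and 1 lb/week is 78/240 = 32.5%, against a typical plateau at 7–10%.

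**4. Threshold-regression definition alone.** A segmented fit (0 to 3 breakpoints chosen by BIC, 25 simulated people per setting, SD 1 and 2 lb) gave these shares of Yes among completers:

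- clear flattening: 100%
- very gradual flattening (10% loss, time constant 40 weeks): 36–44%
- loss turning directly to regain: 0–8%
- slowing to 0.35 lb/week: 0%
- steady loss of 0.75 lb/week: 0%

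The fit can pass from a loss segment to a regain segment with none inside the band. The last three kinds of curve are almost always No here and almost always Yes in step 3 at the same noise levels.

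**5. What a near-constant outcome can show.** Take 40 people, a predictor split at its median (20/20), and all k No values in one half, the most favourable case. The two-sided Fisher P is 2 × C(20,k)/C(40,k): 0.49 for k = 2, 0.23 for k = 3, 0.106 for k = 4, 0.047 for k = 5. With 90% or more scoring Yes (k ≤ 4), significance on such a split is impossible.

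**The case against.** The strongest reply is that the real-time rule is not the one that counts. Threshold regression was adopted because real-time plateaus can prove false, and the remote-weighing section makes it final. Under it, fully followed participants can score No, so the outcome can discriminate. This stands in part: it rules out saying that everyone must score Yes, or that No simply means dropout. It does not settle the matter, because the sentence about final assignments concerns visits, while Aim 3 lists both definitions with equal standing.

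A reader might also infer from "A sample size of N = 40 at active weight loss and plateau", from 43 at plateau in Aim 2, and from "A sample size of N = 40 participants who achieve active weight loss" that the plan itself expects no one in the No group. The document does not support that. These are the sizes at which power is quoted for each aim, not a participant flow. Read as a flow they conflict, since 43 at plateau cannot come from 40 active losers. Ninety adults are to be studied, and the number of active losers is not fixed at 40.

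Nor does Aim 3 fail to address early entry. The paired time-to-entry outcome does so directly, and Aim 3 is exploratory, which limits the consequence. How incomplete follow-up is coded may be set out in a fuller plan that is not shown. The competing definitions and the missing horizon, however, are in the text as published.

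**Conclusion.** The point holds in a bounded form. Under the real-time definition, or if either suffices, Yes/No is nearly constant among active losers followed for 18 months: 99.9–100% Yes for flattening, slowing or moderately regaining curves. The remaining No values would come largely from incomplete follow-up. Under threshold regression alone the outcome varies, and it can reverse the classification of the same person. Aim 3 does not choose between them, and the 91% power does not cover this outcome.

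The simulated shares rest on an assumed weight, daily SD and curve shapes. Near-universal entry is an inference from the rule, not a rate the document states. The actual number of No values cannot be derived from the document; the Fisher results show only what follows if it is four or fewer in 40.

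**What to change.** Define plateau entry for Aim 3 by the final threshold regression alone, in line with the remote-weighing section. Analyse it as time to entry, with participants who have not entered censored at their last observed weight, and let this replace the separate ever/never outcome.

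If a dichotomy is kept, fix an early horizon such as the end of the 24-week program. Treat people not observed to that date as censored rather than No, and state that the 91% power does not apply.

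The cost is a change to one outcome definition, using weights already collected. Any dichotomy depends on the chosen horizon, and the document gives no basis for predicting how many would have entered by then, so time to entry should be the main analysis. The 91% was stated for a continuous outcome, so it should also be rechecked once censoring is allowed for.

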**Fig 1 pone.0354678.g001:**
[figure not shown]
Conceptual model of the ADAPT study. Behavioral weight loss involves lifestyle modifications sufficient to cause negative energy balance and weight loss. A substantial percentage of individuals undergoing behavioral weight loss will experience a weight loss plateau—an involuntary cessation of weight loss and restored energy balance at a reduced weight. The ADAPT study is designed to assess physiological changes during weight loss in real-time. The hypothesized changes in energy efficiency and appetite could make achieving additional weight loss more challenging and promote involuntary weight regain.

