The real-time slope of daily percentage of weight change over the preceding 21-day period is monitored on a rolling basis. Participants who meet or exceed their personalized calculated active weight loss slope (equivalent to ≥0.5 lb/week) for the proceeding 21-day period are eligible to be invited for an active weight loss visit once they pass a minimum time threshold of 4 weeks of participation in the behavioral weight loss program. The 4-week minimum criterion is meant to avert acquiring study outcome measures during the early weight loss phase [19]. Participants are determined to be in an involuntary weight loss plateau when their real-time slope over the preceding 21-day period meets their personalized calculated plateau slope (equivalent to within ±0.25 lbs/week; See Fig 4 A and B for representative examples). Participants are only eligible to meet plateau criteria if they previously met active weight loss criteria. When participants meet either criterion, an in-person study visit for the appropriate visit type is scheduled within two weeks.

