**Fig 5 pone.0354678.g005:**
[figure not shown]
ADAPT study design for individualized outcome assessments and study visits corresponding to phases of weight loss. Following phone screening procedures, all participants complete in-person screening and baseline visits. After final eligibility is confirmed, all participants enter into the 24-week behavioral weight loss program, followed by a 1-year observational follow-up period. Remote questionnaires (Qx) are completed at week 8, 16 and 24 of the behavioral weight loss program, then during the observational period at 9-, 12-, 15- and 18-months from baseline. Daily weights are transmitted remotely to study staff after the baseline visit and continuously monitored throughout the 18-month enrollment period. Individual slopes of weight change are continuously calculated in real-time on a rolling basis over the previous 21-day period. Once a participant is determined to meet real-time criteria for an in-person study assessment, visits for the appropriate study phase are scheduled within 2 weeks of when the participant was identified as meeting study criteria. The participant may be invited to complete a supplemental plateau visit (occurring over 2 days) if interim threshold regression modeling fails to confirm a plateau phase at the time of their initial plateau visit.

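### Aim 3 treats time to plateau as an ordinary continuous outcome, although it is right-censored in anyone who has not plateaued by 18 months or stops weighing

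*Protocol article*

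**What the plan says.** The Aim 3 paragraph of the statistical analysis plan names two outcomes. One is a Yes/No indicator of whether a plateau occurs. The other is the "time from baseline (beginning of behavioral weight loss program) to plateau entry (continuous"). It sets the analysis population: "Analyses will include only participants who achieved active weight loss". It gives one power statement, limited to outcomes of the second type: "N = 40 participants who achieve active weight loss provides 91% power to detect effect sizes of R^2^ ≥ 0.36 at P < 0.05 for continuous". No survival model, censoring rule or treatment of participants without a plateau time is mentioned.

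Three other places bear on whether everyone will have a plateau time:

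- The section on remote weighing and real-time classification states: "Participants are only eligible to meet plateau criteria if they previously met active weight loss criteria". Participants with a plateau are therefore a subset of the active losers.
- The Fig 5 legend says that daily weights are "continuously monitored throughout the 18-month enrollment period", which fixes the end of observation.
- The Fig 1 legend says: "A substantial percentage of individuals undergoing behavioral weight loss will experience a weight loss plateau". That is not all of them, and no percentage is given.

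The Introduction frames the Aim 3 hypothesis around early entry into a plateau, which is a question of timing.

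**The concern.** A plateau time exists only for participants seen to plateau. For someone still losing at 18 months, or whose weights stop arriving, it is known only to exceed the time observed. Labelling the variable continuous and sizing it by R² fits an outcome observed in everyone.

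The two outcomes also pull against each other. If every active loser plateaus, the Yes/No outcome has no one in the No category and cannot be modelled. If some do not, the continuous outcome cannot have 40 values from 40 active losers. The Yes/No outcome does not repair this, because it discards timing and does not by itself separate a No after 18 months of observation from a No after a few months.

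What is at stake is the contrast that Aim 3 needs. The participants who lose weight longest are the natural comparison for early entry, and they are the ones without a time. Leaving them out selects on the outcome, which flattens predictor slopes and costs power.

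**Working it through.** **Inputs from the protocol.** N = 40 active losers, R² = 0.36, two-sided P < 0.05, stated power 91% (Aim 3); observation ends at 18 months (Fig 5 legend). The number of predictors and the share of active losers who never plateau are not given, so both are varied below.

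**1. The plan's 91%.** For the overall F test in linear regression with u predictors:

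- f² = R²/(1 − R²) = 0.36/0.64 = 0.5625
- noncentrality = f² × N = 0.5625 × 40 = 22.5, with u and 40 − u − 1 degrees of freedom

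Power is 99.6% for u = 1, 94.3% for u = 5, 92.2% for u = 6, 89.8% for u = 7 and 87.3% for u = 8. The stated figure is therefore consistent with about 6 or 7 predictors (an inference) and with 40 observed plateau times. With u = 6 and R² held at 0.36, 36 observed times give 88%, 32 give 82% and 28 give 73%.

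**2. Slope and R² when only observed times are regressed.** Assume that predictor and plateau time (on a suitable scale) are jointly normal with correlation ρ, ρ² = 0.36, and that a share p plateaus by 18 months. Let z = Φ⁻¹(p), λ = φ(z)/p and δ = λ(λ + z). Then

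- variance of the observed times, relative to all times = 1 − δ
- slope recovered, as a share of the true slope = (1 − δ)/(1 − ρ²δ)
- R² among observed = ρ² × that share

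For p = 0.95: z = 1.645, λ = 0.1086, δ = 0.1904; the share is 0.8096/0.9315 = 0.87 and R² = 0.31. For p = 0.70: z = 0.524, λ = 0.4967, δ = 0.5072; the share is 0.4928/0.8174 = 0.60 and R² = 0.22.

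| Plateau by 18 months (assumed) | Slope recovered | R² among observed |
|---|---|---|
| 95% | 0.87 | 0.31 |
| 90% | 0.79 | 0.29 |
| 80% | 0.69 | 0.25 |
| 70% | 0.60 | 0.22 |

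Simulation gives the same values to within 0.01.

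**3. Power for one predictor.** Simulation with 40 active losers under the same model, comparing least squares on observed times with Cox regression on all 40:

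| Plateau by 18 months (assumed) | No early leaving: least squares / Cox | 15% assumed to leave early: least squares / Cox |
|---|---|---|
| 90% | 93% / 98% | 91% / 96% |
| 80% | 85% / 98% | 83% / 97% |
| 70% | 73% / 97% | 71% / 96% |

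With 95% plateauing and no early leaving the figures are 96% and 97%, so there is then little to choose on power. Simulation error is about 1 to 2 points.

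**4. Early leaving on its own.** With almost no censoring at 18 months and 20% to 40% leaving at random times, the slope ratio is 0.996 to 1.00. When leaving depends on the predictor, the ratio ranged from 0.85 to 1.04 across the plateau-time distributions tried; the lower values also include some censoring at 18 months.

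**The case against.** The strongest reply is that the plan nowhere says participants without a plateau are excluded. Aim 3 names no regression model, the word continuous stands beside Yes/No as a variable type, and the stated population is all active losers. A reader might infer that non-plateauers are dropped, or that a person lost at month 4 is counted as a No; neither is written. This stands, so the attenuation above is conditional on regressing observed times only. It does not remove the point: the data type and the R² power basis are stated, and they suit an uncensored outcome. This is a choice made in the text, not a detail left to a fuller plan.

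Second, few active losers may lack a plateau time. A rolling slope that moves from loss to regain will normally cross the plateau band, and Aims 1 and 2 plan on 40 and 43 participants at plateau. If 40 or more times are observed, the power statement is largely met. So a reader who concludes that the 91% is simply wrong goes too far; it rests on an unstated assumption. Bias from those who never plateau would remain.

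Third, a reader might infer that early leavers also pull every slope towards zero. Step 4 does not support that.

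Fourth, a Cox model run from program start would have its own fault. Active losers cannot plateau before meeting active-loss criteria, which takes at least 4 weeks, and several predictors are measured after baseline. This is correct, and the fix allows for it.

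**Conclusion.** The point holds in a limited form. Time to plateau is right-censored at 18 months and at the last transmitted weight, and Aim 3 labels and powers it as though it were observed in all 40 active losers. If it is analysed only in those who plateau, censoring at 18 months leaves about 0.87 to 0.60 of the true slope and lowers R² from 0.36 to about 0.31 to 0.22. This rests on an assumed 5% to 30% without a plateau, a true R² of 0.36 and a linear model with normal errors; a more skewed distribution of times would change the size.

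The documents do not support the broader readings that non-plateauers are excluded by design, that all loss to follow-up biases towards zero, or that Aim 3 is necessarily underpowered. Severity is moderate: Aim 3 is exploratory, and neither Aim 1 nor Aim 2 depends on it.

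**What to change.** - **Outcome and model.** Replace the Yes/No and continuous outcomes by one time-to-event outcome, plateau entry, analysed by a Cox or discrete-time hazard model in all who achieved active weight loss. Censor at the last transmitted weight or 18 months, whichever is earlier.
- **Start of risk.** Begin risk time when active-loss criteria are met, by delayed entry or a landmark, so that the event-free period before that point does not count as time at risk.
- **Later predictors.** Enter predictors measured after baseline, such as the slope of the first active-loss period, changes in respiratory capacity and trends in craving, as time-varying covariates or from a landmark.
- **Event definition.** Aim 3 allows two definitions of plateau entry (real-time criteria, or the first plateau day from threshold regression). Name one as the event and use the other in a sensitivity analysis.
- **Power.** Restate the 91% in terms of the expected number of plateau events, or say that it assumes 40 observed plateau times, and give the number of predictors.

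The cost is a change of analysis wording and slightly more modelling work. Hazard ratios replace R² as the reported measure. No new data are needed.
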